### Participant timeline {13}

The trial is pragmatic in nature and requires no additional visits or assessments.

#### Randomisation

At the time of consent, a full gynaecological and obstetric clinical history of the woman will be taken. These details should be recorded on the Randomisation Notepad (CRF 1) prior to randomisation as these will be needed for minimisation. This form also contains a checklist for eligibility into the trial and is completed prior to randomisation.

#### Cerclage Placement

The local approved designated C-STICH staff member should report details of the cerclage placement procedure using the Cerclage Placement Form (CRF 2), providing information to include the taking of a microbiological swab, use of and type of antiseptics, technique used, the suture thread used, the number of “bites”, the position of any knots, and use of any tocolytic agent.

#### Cerclage Removal

Please use the Cerclage Removal form (CRF 3) to record details of the removal of sutures. The Cerclage Removal form has been designed to also collect information about further cerclages that have been placed since placement of the initial cerclage.

#### Microbiology Assessment

The Microbiology Assessment form (CRF 4) should be used to record outcomes of microbiology investigations done on any swabs and suture thread/s taken. Please use a separate case report form to record microbiology outcomes for either the high vaginal swab or the removed suture/s.

#### Pregnancy Outcome and Maternity Outcome

The Pregnancy Outcome and Maternity Outcome forms (CRF 5, PART A and PART B) should be used to record the primary outcome and secondary maternal outcomes at the conclusion of the pregnancy.

#### Baby Outcome

Please use the Baby Outcome form (CRF 6) to record information about the baby’s status. Only complete this form where you recorded a “live birth” on CRF 5, PART A, the Pregnancy Outcome form.

The end of neonatal follow-up will be different for neonates born preterm compared with term.

For preterm neonates (born less than 37 weeks), the end of trial follow-up will be the estimated date of delivery (as confirmed by first trimester ultrasound) or discharge from hospital whichever occurred sooner.

For term neonates (born after 37 weeks), the end of trial follow-up will be 28 days post-delivery or discharge from hospital whichever occurred sooner.

The baby outcome form should be completed at either of the above time points or at discharge from hospital whichever is soonest.

The end of trial for the *mother* will be 28 days post-delivery or death, whichever occurred sooner.

The study will be deemed complete when all participants and their neonates have reached the defined time points.

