### Outcomes {12}

C-STICH collects all the outcomes detailed in the core outcome set for preterm birth [4]. The primary outcome measure is pregnancy loss (miscarriage and perinatal mortality, including any stillbirth or neonatal death in the first week of life). A key secondary outcome in the C-STICH trial is time from conception to pregnancy end (any reason). Other maternal and foetal secondary outcomes include:

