#### Neonatal

Early neonatal death (defined as a death within 7 days after delivery)Late neonatal death (defined as a death beyond 7 days and before 28 days after delivery)Birth weight adjusted for gestational age and sex (in live births ≥24 weeks)Small for gestational age and sex (<10th centile, in live births ≥24 weeks)Resuscitation at birth/additional care required (SCBU/NICU/HDU/transitional)/length of stay in additional care (in live births ≥24 weeks)Antibiotics within 72 h/sepsis (clinically diagnosed/proven) (in live births ≥24 weeks)Early neurodevelopmental morbidity (severe abnormality on cranial ultrasound scan) (in live births ≥24 weeks)Respiratory support (ventilation/CPAP)/days on respiratory support (in live births ≥24 weeks)Supplementary oxygen requirements at 36 weeks post menstrual age(in live pre-term births ≥24 weeks, <36 weeks)Necrotising enterocolitis (Bell’s stage 2 or 3) (live pre-term births ≥24 weeks, <37 weeks)Retinopathy of prematurity requiring laser treatment/disabilities/congenital abnormalities (live pre-term births ≥24 weeks, <37 weeks)Serious adverse events

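### Baby follow-up may end at hospital discharge, before the 7-day and 28-day death windows close, and nothing requires a later check of vital status

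*Protocol article*

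**What the plan says.** **Outcomes.** Under Outcomes {12}, the primary outcome is a composite of miscarriage and perinatal mortality, "including any stillbirth or neonatal death in the first week of life". The neonatal list has early neonatal death, up to 7 days, and then: "Late neonatal death (defined as a death beyond 7 days and before 28 days after delivery".

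**End of follow-up.** Under Participant timeline {13}, Baby Outcome, follow-up of term babies is defined so that "the end of trial follow-up will be 28 days post-delivery or discharge from hospital whichever occurred sooner". For preterm babies, "the end of trial follow-up will be the estimated date of delivery", again unless they leave hospital first. The form follows the same clock: "The baby outcome form should be completed at either of the above time points or at discharge from hospital whichever is soonest". The mother, in contrast, is followed to 28 days after delivery or death, with no cut at discharge. The study counts as complete once mothers and babies have reached these points.

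**Other routes to a later death.**
- The form that records the primary outcome (CRF 5) is completed when the pregnancy ends.
- The adverse event section sends neonatal deaths more than 48 hours after the cerclage to the pregnancy outcome form. It closes baby SAE reporting at the defined end of the trial.
- There are no extra visits, and data come from routine notes.
- Continuing-care arrangements and the stated purpose of the stored identifiers both concern delivery at another hospital.

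**The concern.** An outcome defined over a fixed time window needs follow-up at least as long as that window. Here the primary outcome needs the baby's status to day 7 and late neonatal death needs it to day 28, but follow-up may lawfully stop at discharge. This is a mismatch between two stated rules, not a detail left to the analysis plan.

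Two things are at stake. First, one component of the primary outcome is not secured as defined. If a form closed at discharge shows a live baby, the record need not look incomplete, so the planned missing-data sensitivity analysis might not reveal the gap.

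Second, the length of observation depends on length of stay, and so on gestation at birth. The Background suggests that a monofilament suture may act by preventing early delivery. If one arm has longer pregnancies, its babies would tend to go home sooner and be observed for less time.

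**Working it through.** **1. Windows against follow-up**

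| Item | Needs status to | Stated follow-up, discharge on day d |
|---|---|---|
| First-week death (primary) | day 7 | stops at d; gap if d < 7 |
| Late neonatal death | just before day 28 | stops at d; gap if d < 28 |

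A term baby discharged on day 2 has no stated cover for the rest of the first week and none for the late window.

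**2. Does the due date also cut the windows?** This limit applies to preterm babies only. Days from birth to due date = 280 − gestational age in days.
- 36+0: 280 − 252 = 28, so no cut.
- 36+1: 280 − 253 = 27, which is 1 day short.
- 36+6: 280 − 258 = 22, which is 6 days short.

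The due date therefore shortens only the late-death window, by 1 to 6 days, for babies born at 36+1 to 36+6 who are still inpatients. The smallest gap is 22 days, so it never touches the 7-day window.

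**3. Number of primary events.** The article gives no pooled event rate, so it has to be back-solved. The method was first checked against the original target, using the usual two-proportion formula (pooled variance under the null, two-sided 0.05, power 0.90, no continuity correction):

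n per arm = [1.96·√(2p̄(1−p̄)) + 1.2816·√(p₁(1−p₁)+p₂(1−p₂))]² / (p₁−p₂)²

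- With 19% and 11.2%, n = 441 per arm, or 882 in total. With 2.5% attrition, 882/0.975 = 905, against the stated 900. The method reproduces the plan closely.
- With a 41% relative reduction and a total of 2050, the implied braided rate is about 9.0% with no attrition (pooled about 7.1%) or 9.2% with 2.5% attrition (pooled about 7.3%).
- Expected events: 2050 × 0.975 ≈ 2000, and 0.073 × 2000 = 146.

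**4. Primary events at risk of being missed.** Assumptions, none from the article: 70% to 80% of births at term, discharge on days 1 to 3, and 0.2 to 1 post-discharge deaths per 1000 by day 7.
- Term babies: 0.70 × 2000 = 1400 to 0.80 × 2000 = 1600.
- Deaths outside follow-up: 1400 × 0.0002 = 0.3 to 1600 × 0.001 = 1.6.
- Share of events: 0.3/146 = 0.2% to 1.6/146 = 1.1%.

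**5. Effect on power.** Illustration with a braided rate of 9.0%, a 41% reduction and 1025 per arm. Both rates are multiplied by (1 − m), where m is the share of events missed equally in both arms.
- m = 0: 90.05%
- m = 1%: 89.74%
- m = 5%: 88.41%

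The loss is about 0.3 points at 1% and 1.6 points at 5%. The required sample size is not in question.

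**6. Late neonatal death.** On the same assumptions, 1400 to 1600 of about 2000 babies have no stated cover for any of the late window. The number of deaths affected cannot be given, because the article has neither discharge times nor late death rates.

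**The case against.** The strongest reply is that the gap hardly matters for the primary outcome. Miscarriage, previable death and stillbirth occur at or before delivery, and deaths in hospital are seen. Only a baby well enough to go home who then dies within the week falls outside. This stands, and step 4 agrees with it.

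A reader might infer that deaths after discharge are scored as survival, or that every late death after discharge is missed. The article says neither. The primary outcome sits on CRF 5, not on the baby form whose timing is tied to discharge. The sentence that routes neonatal deaths to the pregnancy outcome form has no discharge limit of its own. The mother is followed to day 28, and routine notes may show a later death. Women with missing primary outcome data are left out in the first instance, not counted as survivors. The supportable statement is that status after discharge is not secured. These routes are opportunities, and none is a required check.

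The between-arm argument is also limited for the primary outcome. If at most about 1.6 events are missed across both arms, the difference between arms cannot exceed that on the same assumptions. It carries more weight for late neonatal death, where most of the window may be uncovered.

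**Conclusion.** The mismatch is real: the stated follow-up of the baby is shorter than two of the outcomes it must support, and no other section of the article closes the gap. It should be fixed, but it does not threaten the primary conclusion. A reader might take it as a serious flaw in the primary outcome. The figures do not support that: about 0 to 2 of roughly 146 events. This rests on the assumed term share, discharge days and post-discharge death rate, and on the back-solved pooled rate of about 7.3%.

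The main damage is to late neonatal death. As follow-up is written, it is in effect death before discharge within the window, with observation time that varies with gestation and could differ by arm. The due-date limit adds little, and only for inpatients born at 36+1 to 36+6.

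**What to change.** Separate vital status from morbidity follow-up. State that vital status at 7 and 28 completed days is ascertained for every live-born baby regardless of discharge, from routine records, at the mother's existing 28-day close-out. Keep the present end points (discharge, due date or 28 days) for morbidity items only.

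The baby's NHS or CHI number is already stored and could serve for this check if consent and approvals cover it. The article's stated purpose for the identifiers is narrower, namely tracing women who deliver elsewhere, so this must be confirmed first.

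If the check is not possible, redefine the first-week component and early and late neonatal death as deaths before discharge within each window, and report this as a limitation.

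The cost is one records check per live-born baby and possibly a small amendment. No visit and no change in sample size is needed. Recruitment has closed and the article describes the trial as in follow-up, so whether all babies can still be checked before analysis has to be established.

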### Sample size {14}

The original sample size for C-STICH was informed by a meta-analysis of audit data, with allowance for the fact that this evidence was non-randomised. The pregnancy loss rate was 7.1% with monofilament sutures compared to 19% with braided sutures, a relative reduction of 66% (risk ratio (RR) 0.34, 95% confidence interval (CI) 0.18 to 0.63). A total sample of 326 women would be sufficient to detect a difference of this size with 90% power (*p*=0.05). However, we inflated this to a total sample target of 900 (including inflation for an attrition rate of 2.5%) which enabled us to detect a more plausible relative reduction of 41% (19% with braided to 11.2% with monofilament) with 90% power (*p*=0.05).

Given that there was uncertainty around the estimates used for the rates of pregnancy loss, it was agreed that the Data Monitoring and Ethics Committee (DMEC) would monitor the overall (pooled) event rate throughout the study to assess any deviation from the original sample size assumptions. In July 2017, the DMEC disclosed that the current estimate of the pooled event rate was lower than anticipated and may affect the trials ability to detect a difference between groups, should one exist. They advised that to maintain 90% power to detect the same relative reduction of 41% the sample size should be increased to 2050 women.

### Recruitment {15}

Recruitment will be achieved by a large network of 75 maternity sites across the UK approaching all women undergoing an elective or ultrasound indicated cervical cerclage. Eligible participants will be identified through specialist preterm birth clinics where appropriate to ensure recruitment target are met. Recruitment commenced in August 2015.

### Assignment of interventions: allocation

#### Sequence generation {16a}

Participants should be randomised just prior to the cervical cerclage procedure, to minimise the number of withdrawals and protocol violations, but allowing sufficient time for the obstetrician to prepare the sutures for the procedure. Birmingham Clinical Trials Unit provide a bespoke web-based randomisation with telephone back-up. Patients are entered and randomised into the trial by logging into secure online webpage available at www.birmingham.ac.uk/C-STICH. Each GCP-trained researcher eligible to randomise will be provided with a unique username and password. The online randomisation is available 24 h a day, 7 days a week apart from short periods of scheduled maintenance and when there are occasional network interruptions. Alternatively, investigators can make a Freephone telephone call (Tel - [name]) to the randomisation service. This telephone randomisation service is available between 0900 and 1700 h Monday to Friday.

A Randomisation Form (CRF1) should be used to collate the necessary information prior to randomisation. All eligibility criteria and baseline data items on CRF1 will need to be answered before a trial number and allocation can be given. If an essential data item is missing, randomisation will be suspended but can be resumed once the information is available. This will be followed by a confirmatory email sent to the randomising person, local Principal Investigator, and the main research staff member within the centre.

Women will be randomised in a 1:1 ratio to either monofilament or braided suture material. A minimisation algorithm will be used to ensure balance in the treatment allocation by site, indication for cerclage (a history of ≥3 previous midterm losses or premature births (≤28 weeks)/insertion of a cervical suture in a previous pregnancy/a history of mid trimester loss or premature birth with a (current) shortened cervix (≤25mm)/women whom clinicians deem to be at risk of preterm birth either by history or the results of an ultrasound scan), technique planned (with bladder dissection/without bladder dissection), and intention to commence patient on progesterone (yes/no). A “random element” will be included in the algorithm, so that each participant has a probability (unspecified here) of being randomised to the opposite treatment that they would have otherwise received.

#### Concealment mechanism {16b}

Randomisation will be provided by a secure 24/7 online central randomisation system and a back-up free telephone randomisation service (available during working hours).

#### Implementation {16c}

A minimisation algorithm will be used to ensure balance in the treatment allocation by site, indication for cerclage (a history of ≥3 previous midterm losses or premature births (≤28 weeks)/insertion of a cervical suture in a previous pregnancy/a history of mid trimester loss or premature birth with a (current) shortened cervix (≤25mm)/women whom clinicians deem to be at risk of preterm birth either by history or the results of an ultrasound scan), technique planned (with bladder dissection/without bladder dissection), and intention to commence patient on progesterone (yes/no). A “random element” will be included in the algorithm, so that each participant has a probability (unspecified here) of being randomised to the opposite treatment that they would have otherwise received.

### Assignment of interventions: blinding

#### Who will be blinded {17a}

Clinicians cannot be blinded to the allocation. Should suture allocation need to be recorded in the hospital notes to facilitate the placement of the correct randomised suture (e.g. as cerclage is to be performed later by a different clinician), this is acceptable. The suture material used should also be documented within the operation notes. As far as possible, it is preferable that the patient and microbiologists should remain unaware of the treatment allocation. Duration of blinding should continue, where possible, until both mother and baby have reached their respective trial end points (i.e. final follow-up). The primary outcome (miscarriage, stillbirth, termination of pregnancy and neonatal death) is objective and thus should minimise any bias incurred by lack of blinding.

#### Procedure for unblinding if needed {17b}

The suture material used for the cervical cerclage should be recorded on the operation note and this can be accessed. The surgeon cannot be blinded so unblinding will not occur.

## Data collection and management

### Plans for assessment and collection of outcomes {18a}

Data will be collected from the routine medical notes. The sponsor performs independent on site monitoring of patient records to ensure data quality. This is in accordance with a detailed monitoring plan that is available on request with approximately 10% of the clinical records reviewed in detail.

### Plans to promote participant retention and complete follow-up {18b}

The trials team ensures that all outstanding data is queried monthly with all sites. Where babies are not delivered at the site in which the cerclage was performed, follow-up is facilitated through a continuing care site setup processes.

### Data management {19}

Personal and sensitive data will be collected directly from trial participants’ hospital notes. Participants will be informed about the transfer of this information to the C-STICH Study Office at BCTU and asked for their consent. With the patient’s consent, their name, date of birth, National Health Service (NHS) or Community Health Index (CHI) number of both mother and baby, and Hospital number will be securely stored on the trial database. This will enable tracing of women who deliver in a different hospital.

Patients will be identified using only their unique trial number to verify identity on the data collection forms and in any correspondence between the C-STICH Study Office and the participating site.

Consent forms will be collected by the C-STICH Study Office and stored securely in the Trial Master File (TMF). These forms will be available to various regulatory bodies for inspection upon request.

Data collected will be entered onto a secure computer database, either directly by the local site *via* the internet using secure socket layer (SSL) encryption technology, or indirectly from paper forms by C-STICH study office staff. Regardless of whether completing paper or electronic CRFs, only site staff designated the responsibility on the delegation log can do so—in instances where paper CRFs are completed, site staff must provide their name and signature, which BCTU staff will check against delegation log records at the point of receipt. Where data entry is conducted by BCTU staff, data entry quality checks will occur according to predetermined parameters laid out in the Data Management Plan. In addition, a Data Validation Plan will guide BCTU staff in the generation of queries where, for instance, data provided by sites may not fall into any typically expected parameters. The ability to enter or edit site data on the database will only be provided to those site individuals designated the responsibility by their PI on the delegation log. These individuals will receive usernames and passwords and will only have the ability to edit data relating to their site(s). Similarly relevant BCTU staff will also be provided with usernames and passwords but will have the ability to enter/edit data on behalf of all sites, though may only do so in accordance with the Data Management Guidelines. The database will maintain an audit trail of all data entered by any username. BCTU will also adopt a centralised approach to monitoring data quality and compliance. The trial database has been constructed specifically for the trial data and will include range and logic checks to prevent erroneous data entry. Independent checking of data entry will be periodically undertaken on small sub-samples (i.e. data entry quality checks as mentioned above). The trial statistician will regularly check the balance of allocations by the stratification variables.

Trial data will be held on secure BCTU servers, which are backed up periodically.

All staff involved in the C-STICH study, be they clinical, academic, or employees of BCTU, share the same duty of care to prevent unauthorised disclosure of personal information. No data that could be used to identify an individual will be published. Personal data recorded on all documents will be regarded as strictly confidential and will be handled and stored in accordance with the Data Protection Act 1998 and any amendments.

### Confidentiality {27}

All data will be stored and processed under the provisions of the General Data Protection Regulation 2018. Electronic data will be stored on a secure server at Birmingham Clinical Trials Unit (BCTU). Access to participant data is restricted to designated staff at the C-STICH Trial Office and clinicians treating the participants all whom have unique usernames and passwords. Access to the trials unit is by authorised individuals only. All data received in paper format for the trial will be kept in a lockable unit in a secure storage area with access only by C-STICH trial staff.

Published results will not contain any personal data that could allow identification of individual participants.

All investigators and study site staff involved with this study may not disclose or use for any purpose other than performance of the study, any data, record, or other unpublished, confidential information disclosed to those individuals for the purpose of the study. Prior written agreement from the sponsor or its designee must be obtained for the disclosure of any said confidential information to other parties. No data that could be used to identify an individual will be published.

